### Data collection

The study uses a mixed methods data collection approach (quantitative and qualitative). The data sources are client and service provider surveys; data extraction from facility records, G-ANC registers, patient held records; and FGDs and IDIs with providers, women, and sub-national health managers. Phase 1 data collection ended January 2018 in both countries. Phase 2 data collection concludes in October 2018. The two phases of the study use similar data collection approaches.
Table 6 summarizes data collection by phase. Each participant was assigned a unique study ID that is used to link all the data from the same individual in the database. Qualitative data will be used to complement the quantitative data through more in-depth exploration of selected thematic areas.

**Table 6. T6:** Data collection timing and tools, by trial phase. Summary of the timing of when each data collection tools stratified by study phase (1&2).

DATA COLLECTION: TIMING	Intervention health facilities		Control health facilities		Intervention only	
	Tool #		Tool #		Tool #	
	Health care providers	Pregnant women	Health care providers	Pregnant women	Sub-national health managers
**BASELINE**					
**Baseline survey**: at enrollment	1	2	1	2	**-**
**PHASE 1: G-ANC**					
**Phase 1 surveys**: providers after last cohort finishes; women 3–6 weeks postpartum (PP)	3	4	-	4	-
**Data extraction** from G-ANC registers, women-held records and facility records: extracted concurrently with surveys	-	5	-	5	-
**FGDs and IDIs**: toward completion of Phase 1, subset of PP women	6	7	-	-	6
**PHASE 2: HMHB**					
**Phase 2 surveys**: providers after last cohort finishes; women at 12 months PP or after their last HMHB meeting	8	9	-	9	-
**Data extraction** from HMHB registers, women-held records and facility records: extracted concurrently with surveys	-	10	-	10	-
**FGDs and IDIs** at completion of group care during year following birth (n=subset, to saturation)	11	12	-	-	11

**Numbered data collection tools:** 1: ANC baseline survey; 2: survey of recently delivered women; 3: data extraction tool (from G-ANC registers and health facility records); 4: FGD guide for pregnant women in the intervention group at completion of G-ANC meetings; 5: IDI guide for pregnant women, at completion of group care before delivery; 6: IDI guide for health care providers (after completion of group care before delivery); 7: IDI guide for sub-national health managers (after completion of group care before delivery); 8: women's survey at one year after birth; 9: data extraction tool (from HMHB registers and health facility records); 10: IDI guide for women, at completion of group care, approximately 12 months after delivery; 11: IDI guide for health care providers (after completion of group care, approximately 12 months after delivery); 12: IDI guide for sub-national health managers and health facility in-charges (after completion of group care)

Study data were collected and managed using electronic data capture tools hosted at Jhpiego through the
REDCap
^TM^ (Research Electronic Data Capture) platform. REDCap is a secure, web-based application designed to support data capture for research studies.

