**Pregnant women**	• Minimum age of 15 years at the time of enrollment * • Appropriate GA as best estimated by provider using combination of last menstrual period, pelvic exam, fundal height, quickening, ultrasound, and/or timing of fetal heart tones dependent on availability o Control sites: < 24 weeks GA o Intervention sites: Between 20–24 weeks GA at the time of first group meeting; and reply “yes” or “unsure” when asked if can return for first cohort meeting • Willing and able to provide a phone number through which she can be reached • Detailed locator information for follow-up (all who provide cell phone number AND also for those without cellphone but traceable). • Planning to stay in area for the next year, and not planning to be away from home (near this facility) for more than four weeks in a row at any time during pregnancy or more than three months in a row in the year after the baby is born • Willing to participate and consent to follow-up for up to 12 months post-delivery
**Health care** **providers**	• Working in a participating/selected health facility and providing ANC or PNC services • Willing to participate in the study
**Sub-national health** **managers**	• Working in the study state or county as a government official managing health activities and/or service delivery • Willing to participate in the study

*Note, In Kenya, pregnant women under the age of 18 are considered mature minors and are able to give consent for themselves, if they can demonstrate evidence of clear understanding of the requirements for the research they are consenting to participate in Kenya
^45^. In Nigeria, persons aged 13 and above can consent for themselves (i.e., without parental consent) to participate in non-therapeutic research
^46^.

***Eligibility for participants.*** Study participants include pregnant women, health care providers, and sub-national health managers. The inclusion criteria are detailed in
Table 2. There were no additional exclusion criteria.

**Pregnant women**: Pregnant women 15 years and older attending ANC1 in any of the study health facilities. Additional criteria on GA and availability were applied depending on the study arm.

**Health care providers:** Providers working in the participating health facilities primarily providing ANC and PNC services.

**Sub-national health managers:** Included either government officials who work in sub-national level health management positions or health facility in-charge in study settings.

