**G-ANC**		
**Meeting 1**	**20–24 weeks GA** • Introduction to group care • Preventing problems in pregnancy	
**Meeting 2**	**24–28 weeks GA** • Recognizing problems in pregnancy • Partner negotiation and communication (e.g., sexually transmitted infection prevention)	
**Meeting 3**	**28–32 weeks GA: Partners encouraged to attend** (if group agrees) • Birth planning • Healthy timing and spacing of pregnancy and PPFP method options	
**Meeting 4**	**32–36 weeks GA** • Review individual birth plans and PPFP intent • Preventing problems after birth (maternal and newborn) • Labor signs	
**Meeting 5**	**36–40 weeks GA** • What to expect in labor and birth • Recognizing postpartum problems (maternal and newborn)	
HMHB		
**Meeting 1**	**3 months after** **delivery**	Clinical care is offered to babies and mothers at every meeting. Each meeting covers similar topics with content specific to the age of the baby: **Raising Baby** • Understand your baby: Developmental milestones; responsive and positive parenting • Maximize love and learning: Four age-appropriate activities for early childhood development are demonstrated and practiced, including one picture-based, early literacy activity, in each session • Feed and protect: Three to four specific topics covering: nutrition; water, sanitation, and hygiene practices; accident prevention; and well-baby care (e.g., immunizations, vitamin A, use of oral rehydration salts) **Taking Care of Yourself** • Self-care activities: Recognizing postpartum depression; postpartum exercise/pelvic floor rehabilitation; getting rest; asking for help • PPFP: Sharing experiences and knowledge; partner challenges; management of side effects
**Meeting 2**	**6 months after** **delivery**	
**Meeting 3**	**9 months after** **delivery**	
**Meeting 4**	**12 months after** **delivery**	

At the first meeting, women agreed on what day and time they would like subsequent meetings to be and whether husbands should be invited to Meeting 3 (
Table 4). Women who have or develop complications requiring additional individual care are encouraged to continue attending group meetings.

Longitudinal group care registers were introduced in the intervention facilities and used for each cohort. They serve a dual purpose of data collection and reinforcement of key actions by providers and women, such as taking IFA supplements, sleeping under a LLIN, birth planning, and making plans regarding healthy timing and spacing of pregnancy.

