***Phase 2: HMHB.*** Healthy Mother, Healthy Baby meetings extend group care into the first year after birth (
Table 4). The same cohorts continue to meet, with their babies. Meetings are scheduled every three months (total of four HMHB meetings). Because of the staggered timing of births for women in a cohort, HMHB meetings are not designed to replace standard PNC visits (i.e., four visits in the first six weeks) as recommended by WHO and included in national guidelines of both countries
^51^. Women in both arms are encouraged to follow country guidelines regarding immediate PNC, as well as national immunization schedules (when they do not correspond to scheduled group meetings).

In 2017, the G-ANC facilitators were trained to facilitate HMHB meetings and remained attached to the same cohorts in the intervention arm. Prior to the first cohort delivering, two to three providers from each facility in both arms will receive clinical training in PPFP methods.

***Meeting frameworks and key content.*** The meeting frameworks for G-ANC and HMHB were designed to incorporate three key components of group care: 1) individual clinical assessment; 2) participatory, facilitated learning, and; 3) peer support. The frameworks were informed by evidence-based learning principles, social behavior change and communication principles, and social support theories. They were designed to include highly facilitative, nonhierarchical, patient-centered participatory approaches with attention to education and literacy levels and community cultural norms.

Clinical assessments include self-assessments (e.g., blood pressure, weight, and danger signs), and brief, individual, private assessments with the provider, behind screens within the group meeting space. To address the main topic of each meeting, large illustrations cards are used to facilitate discussion around key actions or danger signs. Questions are posed to the group while viewing each illustration to: promote sharing of knowledge, examine cause and effect, agree on actions to take, discuss barriers and solutions, and agree to share information with others. The women receive take-home booklets with small versions of the same illustrations to use as memory aids and resource guides for sharing information with family and friends. Other meeting components are designed to specifically support group identity and cohesion; promote empowerment, self-efficacy, and agency; and promote self-reflection and planned action.

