### Outcomes

Different outcomes are targeted for the different phases of the trial. The primary outcome for Phase 1 is the proportion of facility-based delivery among women enrolled in intervention (G-ANC) arm versus control (standard individual care) arm. For Phase 2, the main outcome is the proportion of women using a modern FP method (defined for study purposes as condoms, oral contraceptives, injectables, implants, IUDs, and sterilization) at 12 months postpartum, comparing the two study arms.

Secondary outcomes include additional measures of: service utilization; provision of quality ANC; experience of care by women and providers (measures of satisfaction and positive experience); MNCH/FP-related health literacy and uptake of healthy behaviors (e.g., sleeping under a LLINs, taking IFA supplements, early initiation of breastfeeding, knowledge of danger signs, knowledge of lactational amenorrhea method criteria); and improvement in agency, self-efficacy, and empowerment, specifically related to birth planning and PPFP (
Table 5).

**Table 5. T5:** Research questions and outcomes by study phase. Study research questions, outcomes and data collection tools stratified by study phase (1&2).

Research Questions	Secondary Research Questions

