### Study status

Enrollment of study participants and collection of baseline data began in October 2016, with the first group meetings occurring at the end of the month. Enrollment was completed in January 2017 in Nigeria and June 2017 in Kenya. Overall 1,075 and 1,013 pregnant women were enrolled in Nigeria and Kenya, respectively.
Figure 2 and
Figure 3 show the enrollment cascade for the two countries.

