**Figure 3. f3:**
[figure not shown]
Enrollment of study participants in Nigeria. CONSORT flowchart of the eligibility screening, consent, and enrolment of study participants in Nigeria.

In Nigeria, G-ANC meetings for Phase 1 were completed in May 2017 with data collection for Phase 1 completed in September 2017. Phase 2 HMHB meetings were completed in May 2018, and data collection in July 2018.

In Kenya, Phase 1 G-ANC meetings were completed in October 2017 and data collection in January 2018. Phase 2 HMHB meetings and data collection will be completed in November 2018. Final study results will be available in February 2019.

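### The Phase 2 survey rule and closing dates do not secure a common 12-month postpartum assessment of family planning use in the two arms

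*Protocol article*

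**What the plan says.** The Outcomes section defines the Phase 2 primary outcome as use of a modern method "at 12 months postpartum, comparing the two study arms", and Table 5 repeats the one-year time point. Table 6 gives one timing entry for the women's Phase 2 survey, covering both arms: "women at 12 months PP or after their last HMHB meeting".

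Healthy Mother, Healthy Baby (HMHB) meetings exist only in the intervention arm. Table 4 places the fourth and last one "12 months after" delivery. The meetings belong to cohorts, however, and the Phase 2 description acknowledges that women in a cohort do not deliver together: "Because of the staggered timing of births for women in a cohort", the meetings are not meant to replace standard postnatal visits.

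Entry rules differ by arm. Table 2 gives "Control sites: < 24 weeks GA" with no lower limit, whereas intervention women must be 20–24 weeks at a fixed first group meeting. Recruitment and consent adds that all eligible and willing control women were consented.

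On dates, Study status says "Enrollment was completed in January 2017 in Nigeria and June 2017 in Kenya". In Nigeria, Phase 2 meetings ended in May 2018 and data collection in July 2018. For Kenya, Study status says "Phase 2 HMHB meetings and data collection will be completed in November 2018", and the Abstract also gives November. The Data collection section says "Phase 2 data collection concludes in October 2018".

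**The concern.** An outcome fixed at 12 months needs the same clock in both arms. Table 6 offers a second clock that only one arm can use and that does not run from the woman's own delivery. The calendar is also tied to enrolment rules that differ by arm. The cohort rule puts an upper limit on how late an intervention woman can deliver. The control rule does not, because a woman could enter in the last month of enrolment at an early gestation.

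FP use changes over the first year after birth. If months since delivery at survey differ by arm, or if some women in one arm cannot reach 12 months before closing, part of the observed difference could reflect timing or missingness. This concerns a primary outcome for which the Sample size section aims at differences of 10 points (Kenya) and 9 points (Nigeria).

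**Working it through.** The plan gives no calculated figure on this point; the inputs are its dates and GA limits. I assume birth at 40 weeks. Dates are given only to the month, so month ends are used unless stated.

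**1. Intervention calendar.** The last antenatal group meeting falls at 36–40 weeks (Table 4), so the latest due date is that meeting plus 4 weeks.
- Nigeria: 31 May 2017 + 4 weeks = 28 June 2017; 12 months on 28 June 2018, inside the July 2018 close.
- Kenya: 31 October 2017 + 4 weeks = 28 November 2017; 12 months on 28 November 2018. This is inside a 30 November close. At a 31 October close such a woman is 11.1 months postpartum.

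The stated calendar therefore fits the cohort rule in Nigeria and, with the November date, in Kenya.

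**2. Control calendar.** Minimum GA at enrolment needed to reach 12 months by closing = 40 − (closing date − 365 days − enrolment date)/7.

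| Country, enrolment date | Closing date | Days available before birth | Minimum GA (weeks) |
|---|---|---|---|
| Nigeria, 31 Jan 2017 | 31 Jul 2018 | 181 | 40 − 25.9 = 14.1 |
| Nigeria, 1 Jan 2017 | 31 Jul 2018 | 211 | 40 − 30.1 = 9.9 |
| Kenya, 30 Jun 2017 | 30 Nov 2018 | 153 | 40 − 21.9 = 18.1 |
| Kenya, 1 Jun 2017 | 30 Nov 2018 | 182 | 40 − 26.0 = 14.0 |
| Kenya, 30 Jun 2017 | 31 Oct 2018 | 123 | 40 − 17.6 = 22.4 |
| Kenya, 1 Jun 2017 | 31 Oct 2018 | 152 | 40 − 21.7 = 18.3 |

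A control woman enrolled on the last day at 12 weeks would be 11.5 months postpartum at closing in Nigeria, and 10.6 (November) or 9.6 (October) months in Kenya.

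**3. Cross-check without enrolment GA.** Phase 1 surveys were due 3–6 weeks after delivery and closed in September 2017 (Nigeria) and January 2018 (Kenya). The last Phase 1 respondents would then have delivered between 19 August and 9 September 2017 in Nigeria, and between 20 December 2017 and 10 January 2018 in Kenya. At Phase 2 closing they are:
- Nigeria, 31 July 2018: 10.7–11.4 months
- Kenya, 30 November 2018: 10.6–11.3 months
- Kenya, 31 October 2018: 9.7–10.3 months

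The largest shortfalls are 12 − 10.7 = 1.3, 12 − 10.6 = 1.4 and 12 − 9.7 = 2.3 months. On the most favourable reading (Phase 1 closing at the start of its month, 6-week survey, Phase 2 closing at the end of its month) the figures become 12.3, 12.3 and 11.3 months. The October date fails even then. This check does not separate the arms, and it assumes that the 3–6 week timing was kept.

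**4. Last HMHB meeting as an anchor.** For Nigeria's last cohort, due dates run from 1 May 2017 (last antenatal meeting on 1 May at 40 weeks) to 28 June 2017 (31 May at 36 weeks). A final HMHB meeting on 31 May 2018 falls at 13.0 to 11.1 months postpartum. The anchor departs from 12 months by weeks, in either direction.

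**The case against.** The outcome is defined at 12 months in both arms and the last HMHB meeting is nominally at 12 months, so the two anchors in Table 6 are meant to coincide. That stands: the article does not say that the arms are timed differently, and the gap is one of weeks, inferred from the alternative wording and the cohort scheduling.

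A reader might infer that intervention women are surveyed just after an FP prompt and that this inflates the effect. The documents do not support this. HMHB meetings, with their FP content, are part of the randomized intervention, so a method started there and in use at 12 months is effect. Only starts after 12 months would be a timing problem, and nothing shows how many there are. In Nigeria data collection ran on to July 2018 after meetings ended in May, so an immediate survey is not established either. No rate of method start at the last meeting is given, so no bias in percentage points can be derived.

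The GA limits describe late enrollees. With the November close, a Kenyan control woman enrolled on 1 May 2017 needs only 40 − 213/7 = 9.6 weeks. Table 1 gives national median GA at first visit of 5.4 months (Kenya) and 5.0 months (Nigeria), which suggests that very early entry is not the rule. Those medians cover all women, however, while the trial took only those below 24 weeks. Neither the enrolled GA distribution nor the last enrolment date by arm is given. So the affected share may be small, but it is unknown.

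A condensed article may leave a survey window to the study manual. True, and the lack of a window is not the point. The article states a timing rule and closing dates that do not secure its own endpoint.

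**Conclusion.** The point holds in limited form. The timing rule and closing dates as stated do not ensure that FP use is assessed at 12 months postpartum alike in both arms. Some control women who enrolled late in the recruitment period and early in gestation would be surveyed roughly 0.5 to 2 months early, or missed. With the July 2018 (Nigeria) and November 2018 (Kenya) closes, the cohort rule still brings the last intervention women to 12 months, so the shortfall falls mainly on controls. With the October date some Kenyan intervention women fall short too, and the problem is not confined to one arm.

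This rests on birth at 40 weeks and month-end dates. The share affected and the direction of bias are unknown. A reader might also infer that timing cannot be disentangled from treatment. That goes too far, because time since delivery can be measured, reported and adjusted for. The closing date (October or November 2018) is a plain contradiction and moves the Kenyan limit by 22.4 − 18.1 = 4.3 weeks of GA.

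**What to change.** 1. Anchor the Phase 2 survey and outcome on 12 months from each woman's own delivery in both arms, with one common window, and remove the last HMHB meeting as an alternative timing anchor. Where the survey falls later than 12 months, derive use at 12 months from method start and stop dates.
2. Keep every observed survey. Setting out-of-window surveys to missing could discard mainly control outcomes. Report months since delivery at survey by arm, with one sensitivity analysis that adjusts for it and one restricted to the window.
3. Reconcile the October and November 2018 closing dates. In Kenya, keep surveys open until the last enrolled woman reaches 12 months, or report by arm how many did not. In Nigeria, where collection is complete, report that count by arm.
4. Reconcile the Abstract, which ends enrolment in June 2017 for both countries, with the January 2017 date for Nigeria given elsewhere. A June end would enlarge the Nigerian shortfall.

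The cost is some added analysis, start- and stop-date items in the survey, and possibly a few more weeks of follow-up in Kenya. By the step 3 dates, the last Phase 1 respondents there reach 12 months between 20 December 2018 and 10 January 2019, which leaves little time before results are due in February 2019.

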***Quantitative data***

**Surveys (
Supplementary File 1)**: Baseline surveys were completed at the time of enrollment, during the woman’s first ANC visit. Face-to-face interviews with recently delivered women (RDW) were conducted at the end of Phase 1 (3–6 weeks post-delivery) to gather information regarding the women’s ANC and delivery experience. For the RDW survey, RAs contacted women by mobile phone to schedule a time to visit them at home to conduct the survey, based on the expected day of delivery, from REDCap
^TM^. RAs made up to five attempts to contact the women on different days of the week at different times of the day over a two-week period to schedule an interview. If phone numbers were not functional or women were not successfully contacted after 5 attempts, physical tracing was done using the information provided at enrollment. Detailed locator information was obtained and authority for home visits at consent stage for all participants who were enrolled.

Women are also scheduled to be surveyed after Phase 2 to collect data on MNCH/FP care received in the 12 months after birth. Data are captured electronically using tablets loaded with REDCap
^TM^ software. During both phases, a participant is determined to be lost to follow-up if both phone and physical tracing efforts are unsuccessful.

**Data extraction:** Per the study protocol RAs extracted data from different sources including: longitudinal group care registers; women-held records (Kenya only); and other relevant facility-based health records. The data were captured electronically through REDCap.

***Qualitative data.*** Focus group discussions and IDIs were scheduled and conducted in 2017 toward the end of Phase 1 and will be conducted toward the end of Phase 2 in 2018. An international qualitative research team lead, trained, and oversaw local qualitative researchers familiar with MNCH/FP-related issues. The FGDs and IDIs were audio-recorded and then transcribed after obtaining consent from the study participants.

**Focus group discussions**: FGDs for health care providers explored attitudes toward providing group care; perceived changes in their communication and relationship with patients; changes in empowerment, self-efficacy, and satisfaction related to their perceived ability to do their job well; sustainability of group care; suggested changes to the model and logistics required to offer group care; and perceived effects of group care on colleagues and clients. For the women attending group care, FGDs explored: satisfaction with care; perceived changes in self-efficacy or empowerment; health literacy; improved communication and trust with providers and health system as a whole; factors in uptake and continuation of PPFP; and overall impression of the group care model. Phase 2 FGDs will focus on similar topics; with a further focus on the ways HMHB influenced beliefs and actions around PPFP, nutrition and early childhood development practices, couple communication, and development of social capital.

**In-depth interviews:** IDIs were conducted with a select group of women on pre-determined topics that might have been difficult to explore through FGDs. To explore how problem recognition and care seeking was influenced by G-ANC, criteria for selection included: non-responders, (i.e., women who only came to one or two meetings [those whose barriers we don’t understand]); women who attended G-ANC meetings but didn’t deliver in a facility; and women who experienced complications during pregnancy. The IDIs are conducted until saturation of new information is reached. In addition, sub-national health managers were also selected for IDIs. Phase 2 IDIs will follow a similar pattern, including inclusion of those who came to meetings but did not accept PPFP at one year postpartum and exploration of care seeking for sick infants.

